## Abstract

**Background:**

As done in combined lifestyle interventions (CLI), a combination of physical activity, diet, and sleep interventions is effective in reducing body mass index (BMI) and hyperglycaemia. The timing of the behaviours during the day may also affect metabolic health, due to individuals’ circadian rhythms, but the impact of this is not well known. Thus, the inclusion of education on the timing of lifestyle behaviours may be an important addition to CLIs. Therefore, we aim to investigate the metabolic health effect of adding education on timing of lifestyle behaviours to an online CLI among adults who have obesity or are overweight with complications, compared to standard CLI, and routine care.

**Methods:**

In this two-armed, cluster-randomized, superiority, pragmatic trial, at least ten CLI counselling groups will be cluster-randomized to either the standard CLI or the TIMED CLI, with added education on the timing of sleep, physical activity, and dietary intake. Among these clusters, we aim to recruit approximately 100 participants. The primary outcome is self-reported BMI at baseline, and at 3, 9, and 24 months. Secondary outcomes are health-related quality of life (HRQoL) measured using a questionnaire, self-reported waist circumference, fasting glucose and HbA1c measured using at-home finger prick testing at baseline, and at 3, and 9 months. Adherence will be assessed through questionnaires and attendance to the CLI sessions. In addition, an observational control group of 800 participants from a routine care database will be included for comparison. Recruitment started in July 2024.

**Discussion:**

To our knowledge, this is the first pragmatic, cluster-randomized trial that investigates the incorporation of education on circadian timing of lifestyle behaviours in a routine care CLI. The pragmatic design will enable the investigation of the feasibility and metabolic health effect of implementing these timed interventions in a routine care setting.

**Trial registration:**

ISRCTN registry, protocol number ISRCTN14642827. Registered on 7 December 2023, www.isrctn.com/ISRCTN14642827.

**Supplementary Information:**

The online version contains supplementary material available at 10.1186/s13063-026-09788-z.

## Administrative information

Note: the numbers in curly brackets in this protocol refer to SPIRIT checklist item numbers. The order of the items has been modified to group similar items (see http://www.equator-network.org/reporting-guidelines/spirit-2013-statement-defining-standard-protocol-items-for-clinical-trials/).

Role of sponsor {5c}	As the sponsor the Amsterdam UMC, location VUmc ‘ Stichting VUmc’ is responsible for the study design, data collection, management and analysis and publication of the result. The funders have been involved in the concept of the study design.

## Introduction

### Background and rationale {6a}

The prevalence of overweight and obesity has been steadily rising over the past several decades, increasing the risk of chronic diseases, such as type 2 diabetes, and decreasing health-related quality of life (HRQoL) [1]. Lifestyle behaviours, such as unhealthy dietary patterns, physical inactivity, and poor sleep are associated with increased risk of overweight and obesity [2, 3]. Improving these behaviours can prevent and reduce overweight, obesity, and associated chronic diseases [4–12].

Combined lifestyle interventions (CLIs) provide education and behavioural change techniques (BCTs) to increase physical activity, improve sleep, and improve diet quality. BCTs regularly used in CLIs are based on the taxonomy of behaviour change techniques by Michi et al. [13], and include the main themes of: goal setting and action planning, providing feedback and mentoring, facilitating social support, and shaping knowledge [14]. Interventions that target a combination of different lifestyle factors have shown to be effective to treat people with obesity, prevent type 2 diabetes, and improve HRQoL [15–26]. Therefore, such CLIs have been implemented in Dutch routine care and are reimbursed for adults who have obesity, or are overweight with one of the following comorbid conditions: type 2 diabetes, vascular diseases, sleep apnoea, osteoarthritis, or increased waist circumference [27].

In addition to the quantity and quality of an individual’s physical activity, food intake, and sleep, the timing of these lifestyle behaviours during the day is important for metabolic health [28, 29]. The human body has various circadian rhythms of roughly 24 h, which are generated in the suprachiasmatic nucleus (SCN) in the hypothalamus. The SCN causes physiological and behavioural rhythms, such as rhythms in the body temperature, hormones, glucose metabolism, and cognition. The SCN is mainly entrained by the light-dark cycle, but is also influenced by external ‘Zeitgebers’, such as artificial light, physical activity, and food intake [30]. In the 24/7 nature of modern industrial societies, disruption of sleep-wake rhythms has become increasingly common, due to the rise of shiftwork, time zone transfers, social jetlag, and exposure to artificial light during nighttime hours. These exposures misalign our circadian rhythms, which is associated with increased prevalence of obesity and related diseases [31–38]. For example, shiftwork has been linked to a 1.17 and 1.10 times higher risk of obesity and diabetes, respectively [39, 40]. Changes to the timing of lifestyle behaviours can, however, show potential benefits for glycaemic and metabolic control. Experimental studies on afternoon or evening exercise, for instance, have shown reductions in glucose levels, compared to morning exercise [41, 42]. Additionally, both experimental and observational studies show that preventing circadian misalignment contributes to improved glycaemic and metabolic control. Misalignment can be prevented by omitting shiftwork, irregular sleep, or disrupted sleep [24, 39, 43–51], avoiding (blue) light exposure before bedtime [52, 53], and meal-related practices, such as consistent breakfast consumption, avoidance of nighttime snacking, early meal timing, consuming the majority of daily caloric intake early in the day, and a restricted eating window [36, 54–69].

Nevertheless, these studies on altering the timing of lifestyle behaviours are purely mechanistic animal studies; short-term experimental studies in humans (~ weeks), in highly controlled settings, and with detailed mechanistic outlooks; or observational studies in large cohorts, looking at associations of (proxies of) timing of lifestyle behaviours between people, instead of within people. Additionally, these studies focus on only one of the lifestyle behaviours (i.e. only timing of food intake). Previous studies have shown that the combined effects of addressing different lifestyle behaviours are often greater in the treatment of individuals with overweight or obesity on various metabolic risk factors, compared to one isolated behaviour [21, 70–72]. We therefore hypothesize that this combined effect may also be found when combining specific timed lifestyle interventions.

In order to test the additional effects of correctly timed lifestyle behaviours in real life, we will add education on timed lifestyle to an existing Dutch CLI. Currently, a widely used CLI in the Netherlands is the ‘Coaching op Leefstijl’ (CooL; translated as Coaching on Lifestyle) intervention. This intervention is a 2-year programme that consists of monthly group sessions and individual sessions. CooL focusses on identifying unhealthy behaviours (concerning physical activity, nutrition, sleep, stress management, and relaxation), and pitfalls, and provides individualized tools to help change towards healthier behaviours [25]. Consequently, participants may prioritize certain behaviours of CooL over behaviours that are less important for the individual, for example one may focus on nutrition while others focus on sleep. Additionally, Miguide translated the CooL intervention in a digital format for participants that cannot join in person sessions. This Cool-MiGuide intervention has the same design, goals, and elements as CooL, but all group and individual sessions are held online. An 8-month pre-post study on CooL-MiGuide showed positive changes in different behaviours (including sedentary time, diet attentiveness, and sleep), resulting in reduced weight and improved perceived health [73]. Previous studies showed that greater improvements in metabolic markers are seen when the same amount of physical activity, sleep, and meal intake is performed aligned with circadian rhythms, compared to misaligned [74, 75]. Therefore, we hypothesize that adding additional education on timed lifestyle behaviours to CooL-MiGuide will also have greater effects, compared to CooL-MiGuide alone. We assume this behaviour change will directly influence circadian alignment by influencing the SCN, which has biological, psychological, and behavioural consequences that we can measure in the form of positive effects on body weight, glycaemic control, fat distribution, lifestyle behaviours, and HRQoL [30]. The theoretical framework of CooL-MiGuide [76], including education on timed lifestyle behaviour, is depicted in Fig. 1. Accordingly, as is customary for the CLI, the interventions (and also the timed education) are based on education and behavioural change techniques, rather than enforced behaviour change. CooL uses various evidence-based techniques and approaches, including BCTs such as goal setting, mobilizing social support, rewarding, and relapse prevention [13, 25]. The effect on metabolic control is therefore dependent on the adherence to the intervention. Therefore, we will directly measure completion of the modules and attendance to the meetings of CooL-MiGuide, adherence to and changes in timed behaviours, as well as metabolic endpoints. With this, we will be able to conceptualize the working mechanisms and potentially be able to better explain our findings.

**Fig. 1 Fig1:**
[figure not shown]
Theoretical framework of the Cool-Miguide intervention with education on timed lifestyle behaviours

### Objectives {7}

The objective of this study is to investigate the metabolic health effect of adding education on the timing of lifestyle behaviours to an online CLI, compared to the standard online CLI, and routine care, among adults who have obesity or are overweight with complications. The primary outcome of body mass index (BMI), and secondary outcomes of fasting glucose, HbA1c, HRQoL, and waist circumference will be assessed across four timepoints (baseline, and at 3, 9, and 24 months).

### Trial design {8}

This study is a two-armed, cluster-randomized, superiority, pragmatic trial with two comparator groups. At least 10 groups will be cluster-randomized 1:1 to one of the intervention arms: the standard CLI or the TIMED CLI, with added education on timing of lifestyle behaviours. In addition, an additional observational arm will be used for exploratory analyses to distinguish results attributable to the standard CLI from those reflecting additive effects of the timed education in the TIMED CLI. To keep the trial pragmatic and reduce participant burden, instead of active recruitment of a waiting list control group, 800 participants from the routine care database called the Diabetes Management and Treatment (*DIAMANT*) cohort will be included for exploratory purposes only. These exploratory analyses will enable us to distinguish effects attributable to the standard CLI from those reflecting additive effects of the timed education. This cohort, initially for patients with diabetes, recently expanded with all patients with risk factors of type 2 diabetes: cardiometabolic diseases, overweight or obesity, dementia, and depression. These participants will be matched 8:1 based on age, sex, comorbid condition, and postal codes with participants in the two intervention arms.

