### Methods for additional analyses (e.g. subgroup analyses) {20b}

Additional exploratory analyses will be performed to get a better understanding of the effectiveness of the intervention in certain subgroups. Therefore, analyses will be stratified to evaluate whether certain subgroups (e.g., early versus late chronotype, participants with versus without type 2 diabetes) benefit more from the intervention, compared to others. In addition, a greater shift towards desired timing behaviours will be associated with metabolic improvements, to see whether a dose–response relationship can be found. Furthermore, acceptability of the added education will be assessed by comparing the acceptability questionnaire between the standard CLI and TIMED CLI. In addition, the results of the standard CLI and TIMED CLI will be compared with an additional arm from the general care database DIAMANT. It will enable us to distinguish effects attributable to the standard CLI from those reflecting additive effects of the timed education. This is only for exploratory purposes and will not be used to draw any causal conclusions on the effect of the standard CLI itself.

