## Discussion

To date, most research has focused on animal models or short-term experiments in humans (ranging from 24 h to 3 weeks) that examined often single lifestyle factors. Thus, it remains unclear whether improvements in metabolic control can be achieved under real-life by modifying the timing of daily behaviours. Our pragmatic trial will provide insights into whether adding relatively simple education on the timing of lifestyle factors to a CLI can have an additive effect on body weight, glycaemic control, fat distribution, lifestyle behaviours, and quality of life. The pragmatic nature of our study setting enables us to reflect the effect of timed behaviour in real-world conditions, close to routine care. This allows us for an accurate understanding of how these interventions perform in routine care, as opposed to highly controlled experimental settings. This approach offers valuable insights into the feasibility and effectiveness within routine care, enhancing the external validity of the findings. In contrast to current evidence, which mainly relies on highly controlled settings on individual lifestyle factors, our study ensures that results are applicable in real-world settings. Nevertheless, this study design also brings some limitations and points of discussion that should be acknowledged.

First, we include an additional observational arm extracted from the general care database *DIAMANT*. This arm is used for exploratory analyses and can therefore not be used to draw causal conclusions. The arm might inform us on results attributable to the standard CLI from those reflecting additive effects of the timed education. This is an ethical alternative to an additional waiting list control, which maintains the pragmatic nature of the trial and reduces participant burden. However, this database is a non-randomized comparator and has slightly different assessments (i.e. other assays to measure HbA1c) and measuring time points (e.g. one month earlier or later), compared to our study design. We will use matching procedures (1:8 ratio) to minimize baseline imbalances based on age, sex, comorbid conditions, and postal codes, and include participants that have at least two measurement moments over a period of nine months. Nevertheless, residual confounding is always of risk and these comparisons with the observational database should always be interpreted with caution.

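### The exploratory comparison with the DIAMANT routine-care cohort is exposed to avoidable confounding, because the stated matching omits baseline BMI and no BMI entry criterion is applied to the cohort

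*Protocol article*

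**What the plan says.** The Abstract states that "an observational control group of 800 participants from a routine care database will be included for comparison". Trial design {8} gives the matching rule: "These participants will be matched 8:1 based on age, sex, comorbid condition, and postal codes with participants in the two intervention arms". The Discussion repeats it with the same four variables: "We will use matching procedures (1:8 ratio) to minimize baseline imbalances based on age, sex, comorbid conditions, and postal codes". The Discussion adds that the investigators will "include participants that have at least two measurement moments over a period of nine months".

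Trial design {8} describes the source as a cohort first set up for patients with diabetes and "recently expanded with all patients with risk factors of type 2 diabetes: cardiometabolic diseases, overweight or obesity, dementia, and depression". Trial participants, by contrast, must under Table 1 have a BMI of at least 30 kg/m², or of 25 to below 30 kg/m² with a listed comorbid condition. Outcomes {12} makes BMI the primary outcome.

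On the status of the comparison the article speaks in two ways. Objectives {7} names routine care as a comparator with no exploratory label. Trial design {8} and Methods for additional analyses {20b} say the database arm will make it possible to separate what is due to the standard CLI from what the timed education adds. Section {20b} then says the comparison "will not be used to draw any causal conclusions on the effect of the standard CLI itself", and Trial design {8} and the Discussion also call it exploratory.

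**The concern.** When change in BMI is compared between non-randomized groups, baseline BMI is an obvious variable to balance: heavier patients have more to lose, and extreme values tend to drift back towards the mean. The matching list is stated twice in the same form, so it reads as a choice rather than as detail left to a fuller document. If the database patients are lighter at baseline than the CLI participants, the CLI arms could appear to do better than routine care for reasons unrelated to the CLI. The many controls would make such a difference look precise.

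The wording adds to this. A reader of the objective and of the attribution sentences would expect an estimate of what the standard CLI achieves, which the article elsewhere says it will not claim.

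**Working it through.** **The plan's own figure.** The Abstract says "Among these clusters, we aim to recruit approximately 100 participants". Eight matches each gives 8 × 100 = 800, as stated. The comparator size is consistent with the matching ratio, and adding BMI to the matching would leave 800 as the target.

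**Do the listed variables stand in for BMI?** Age, sex and postal code do not fix BMI. Comorbid condition does so only in part. Table 1 lists sleep apnoea, vascular diseases, type 2 diabetes, osteoarthritis and increased waist circumference; only the last is a measure of body size. Under the written rule, a trial participant with type 2 diabetes and obesity could be matched to a database patient with type 2 diabetes and normal weight. A participant who enters on obesity alone needs no listed condition, so that variable may say nothing about the match's weight.

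**Does any passage restrict the cohort by BMI?** The entry groups in Trial design {8} include overweight or obesity, but also groups not defined by weight. The only selection rule given besides matching is the two-measurement condition in the Discussion.

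**Is the follow-up condition the same on both sides?** Database patients need at least two measurements over nine months. Section {20a} analyses the trial arms by intention to treat with mixed models and sets no such condition. This is a difference in selection, not a baseline imbalance, and the documents give nothing from which to size it.

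**How large could the BMI bias be? Illustration only.** The documents give no BMI distribution for either source, so both inputs are assumed:

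- residual gap in mean baseline BMI, D: 1 to 3 kg/m²
- slope of BMI change on baseline BMI, b: 0.05 to 0.20
- bias = D × b: from 1 × 0.05 = 0.05 to 3 × 0.20 = 0.60 kg/m²

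Against the 0.7 kg/m² of Sample size {14} this is 0.05/0.7 = 7% to 0.60/0.7 = 86%. That 0.7 was set for the randomized contrast and serves here only as a yardstick; the article sets no target for the database comparison.

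**Does a large comparator help?** Take the SD of 0.9 from Sample size {14}, and one arm of 50 against its 400 matches, ignoring clustering and matching:

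- SE = 0.9 × √(1/50 + 1/400) = 0.135 kg/m²
- chance of a nominal p < 0.05 from bias alone = 1 − Φ(1.96 − bias/SE) + Φ(−1.96 − bias/SE)
- bias 0.2: about 32%; bias 0.3: about 60%

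With both arms against all 800, SE = 0.9 × √(1/100 + 1/800) = 0.095, and the same biases give about 55% and 88%. More controls shrink the standard error but not the bias.

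**The case against.** The strongest reply is that the comparison is exploratory, that causal conclusions are ruled out, and that the Discussion already calls the database a non-randomized comparator, discloses different assays and time points, and warns of residual confounding. This stands as a limit on severity. It does not answer the point: residual confounding is what remains after matching on the obvious variables, and baseline BMI must be recorded if BMI change is to be compared at all.

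A second reply is that the objective speaks of adults with obesity, or overweight with complications, and that database filters and model covariates may sit in a fuller protocol or SAP. Their absence here is not itself a fault. But the objective is not a selection rule for the database, and even a BMI floor would leave the spread above it unmatched. Section {20c} plans sensitivity analyses that adjust for clinically relevant imbalances; it names neither BMI nor the database arm.

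Third, two measurements is the least needed to observe change, and a trial participant with baseline and one follow-up meets it too. That is fair. The asymmetry may be small, which is why a sensitivity analysis is enough.

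A reader might also infer that the controls are themselves receiving a CLI, since the Background says "such CLIs have been implemented in Dutch routine care and are reimbursed". The documents give no CLI exposure for DIAMANT patients and do not say whether such patients will be excluded, so this remains conjecture.

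**Conclusion.** The point holds as a risk to an exploratory analysis. The stated matching variables omit baseline BMI, no passage applies the trial's BMI criteria to the cohort, and the resulting imbalance is foreseeable and reducible. The attribution wording in Trial design {8} and section {20b}, and the unlabelled comparator in Objectives {7}, disagree with the exploratory, non-causal status stated elsewhere; that part needs no assumption.

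Two stronger readings are tempting and not supported. One is that the comparison is confounded as a matter of fact: the documents show an exposure to confounding, not a realized imbalance, and matching on comorbid condition or later adjustment may remove part of it. The other is that the bias is some known share of the 0.7 kg/m² target: the range of 0.05 to 0.60 kg/m² rests wholly on an assumed baseline gap and slope. The randomized TIMED versus standard CLI comparison, its sample size and its primary analysis are untouched.

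**What to change.** - Restrict DIAMANT candidates to the BMI criteria of Table 1.
- Add baseline BMI to the matching variables, or adjust for it in the model for this comparison.
- Run the comparison with the two-measurement condition applied to trial participants as well, at least as a sensitivity analysis.
- In Trial design {8} and section {20b}, replace the promise to separate effects due to the standard CLI with a descriptive aim, such as setting change in the CLI arms beside change under routine care.
- In Objectives {7}, label routine care as an exploratory comparator.

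This means revised selection and matching code, one further model run and some rewording. Randomization, visits and participant burden do not change. The drawback is that tighter matching may leave some participants with fewer than eight matches, so the comparator may fall short of 800.

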### Eligibility criteria {10}

Eligible study participants are adults with an indication to be referred to a CLI by their general practitioner (Table 1). In addition, participants are excluded if they (1) are unable to provide written informed consent; (2) have serious mental impairment which would prevent them from understanding the study aim; (3) are pregnant; (4) work night shifts; and/or (5) take sulfonylurea medication. The latter is excluded, as the effects of reducing the eating window (part of the TIMED CLI) on the risk of hypoglycaemia in participants taking sulfonylurea medication is not sufficiently known.

**Table 1 Tab1:** Eligibility criteria for inclusion in the pragmatic trial: Indication for referral to a CLI

• Aged 18 years or older • Either (1) obesity (BMI ≥ 30 kg/m^2^); or (2) overweight (BMI ≥ 25 and < 30 kg/m^2^) with at least one comorbid condition: ◦ Sleep apnoea ◦ Vascular diseases ◦ Type 2 diabetes ◦ Osteoarthritis ◦ Increased waist circumference (men ≥ 102 cm; women ≥ 88 cm) • Motivated to change lifestyle behaviour • Digitally skilled and in the possession of a smartphone • Being able to speak and understand the Dutch language	

*CLI *Combined Lifestyle Intervention, *BMI *body mass index

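### The stated rules for selecting the exploratory routine-care comparators use neither the trial's BMI entry criterion nor baseline BMI, so that contrast can include people with no indication for a CLI

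*Protocol article*

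**What the plan says.** The abstract's Methods section announces that "an observational control group of 800 participants from a routine care database will be included for comparison". Trial design {8} names the source as the DIAMANT cohort, which began with patients with diabetes and was "recently expanded with all patients with risk factors of type 2 diabetes: cardiometabolic diseases, overweight or obesity, dementia, and depression". The same section gives the matching rule: "These participants will be matched 8:1 based on age, sex, comorbid condition, and postal codes with participants in the two intervention arms".

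The Discussion states the purpose and the same four variables: "We will use matching procedures (1:8 ratio) to minimize baseline imbalances based on age, sex, comorbid conditions, and postal codes". It adds one further selection rule, to "include participants that have at least two measurement moments over a period of nine months".

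Trial participants enter by a different route. Table 1 under Eligibility criteria {10} requires a BMI of at least 30 kg/m², or a BMI from 25 to below 30 "with at least one comorbid condition". The listed conditions are sleep apnoea, vascular disease, type 2 diabetes, osteoarthritis and increased waist circumference. BMI is also the primary outcome (Outcomes {12}).

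**The concern.** Every trial participant is selected on BMI, but no stated rule selects a comparator on BMI. Overweight or obesity is only one of several ways into DIAMANT; diabetes, cardiometabolic disease, dementia and depression are others, and none of them is said to require a raised BMI. If comorbid condition has its Table 1 meaning, a trial participant with obesity and no comorbidity is matched on age, sex and postal code only, and a match of normal weight is possible.

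Two things are at stake. First, the comparator group need not belong to the population that Objectives {7} names for the routine-care comparison. Second, Trial design {8} and Methods for additional analyses {20b} want this contrast to separate what the standard CLI achieves from what the timing education adds. If the comparators start from a lower BMI, part of the apparent CLI benefit over routine care may only reflect a different starting point.

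**Working it through.** **The plan's own figure.** The abstract says "Among these clusters, we aim to recruit approximately 100 participants". At eight comparators each, 8 × 100 = 800, as stated. The concern is about who the 800 are, not how many.

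**Selection rules side by side**

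| | Trial participants (Table 1) | DIAMANT comparators (Trial design {8}, Discussion) |
|---|---|---|
| BMI threshold | ≥30, or 25 to <30 with a comorbidity | none stated |
| Baseline BMI balanced | by randomisation, between the two CLI arms | not among the matching variables |
| Other rules | motivation, digital skills, language, exclusions | age, sex, comorbid condition, postal code; two or more measurements in nine months |

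**Possible size.** The article gives no BMI distribution for DIAMANT and no correlation over time, so these inputs are assumptions:
- cohort BMI normal with mean μ = 29 and SD σ = 5, with μ from 28 to 30 as a range;
- correlation r between baseline and 9-month BMI of 0.95 to 0.97;
- trial participants drawn from the same distribution, truncated at a cut-off c;
- comparators centred on the cohort mean;
- the selecting reading is also the analysed baseline.

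Share of the cohort below 25: Φ((25 − 29)/5) = Φ(−0.8) = 0.21. For μ = 30 and μ = 28 it is 0.16 and 0.27.

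Mean gap between participants and cohort: σ × φ(a)/(1 − Φ(a)), with a = (c − μ)/σ.
- All entrants at BMI ≥30: a = 0.2, so the gap is 5 × 0.3910/0.4207 = 4.65 kg/m² (participant mean 33.65).
- Entrants across the whole range ≥25: a = −0.8, so the gap is 5 × 0.2897/0.7881 = 1.84 kg/m² (participant mean 30.84).

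Apparent loss from regression to the mean: (1 − r) × gap.

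| Entry mix | r = 0.97 | r = 0.95 |
|---|---|---|
| whole range ≥25 | 0.03 × 1.84 = 0.055 | 0.05 × 1.84 = 0.092 |
| all ≥30 | 0.03 × 4.65 = 0.14 | 0.05 × 4.65 = 0.23 |

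In this model the real mix lies between the two rows, because entrants with BMI 25 to <30 also need a comorbidity. That gives roughly 0.06 to 0.23 kg/m². Letting μ run from 28 to 30 widens it to about 0.04 (gap 1.44, r = 0.97) to 0.27 (gap 5.34, r = 0.95).

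**The case against.** The strongest reply is that the article already limits what this arm can show. Trial design {8} calls it exploratory, section {20b} rules out causal conclusions about the standard CLI, and the Discussion warns of residual confounding and asks for caution. This stands and limits the weight of the point. It does not remove it: a baseline difference in the primary outcome can be avoided at extraction, and the general warning does not name BMI.

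Three stronger readings are tempting but not supported.
- *A reader might infer that the trial's test of timing is biased.* It is not. TIMED versus standard CLI is randomised and does not use DIAMANT. For the same reason, the 0.7 kg/m² in Sample size {14} belongs to another contrast and is not a yardstick here.
- *A reader might infer that the contrast carries the whole baseline BMI gap.* That would hold for a comparison of BMI levels. Section {20a} compares changes, and if those models are also used for DIAMANT, level differences largely cancel. What remains is the dependence of change on baseline.
- *A reader might infer that BMI is certainly ignored.* Comorbid condition is not defined for the matching. If it means the DIAMANT entry conditions, which include overweight or obesity, BMI is partly controlled. Against this, Table 1 lists comorbid conditions separately from BMI, and a yes/no category would not balance BMI level.

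The size is also open to challenge. If the referral reading and the self-measured baseline are separate, some regression occurs before baseline and less remains. Matching on comorbidity may itself pick heavier comparators. The adjusted sensitivity analyses in section {20c} might help, but they are not said to cover the DIAMANT arm, and adjustment cannot give a comparator an indication for a CLI.

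Finally, a condensed article may leave extraction detail to the full protocol. Here, however, the same matching variables are stated twice, together with their purpose, so the point concerns a stated choice.

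**Conclusion.** The point holds for the exploratory CLI-versus-routine-care contrast only. The stated rules do not place the comparators in the population that the Objectives name, and they leave the baseline value of the primary outcome unmatched. Under the assumptions shown, regression to the mean alone would favour the CLI by roughly 0.06 to 0.23 kg/m². The upper end requires all participants to enter at BMI ≥30. Every input to that range is assumed, so it indicates scale and is not an estimate for this trial. Any further dependence of weight change on starting BMI would come on top and is not quantified here. This is a worthwhile, inexpensive improvement and does not threaten the trial's main conclusion.

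**What to change.** 1. Restrict the DIAMANT pool to people who meet the Table 1 BMI and comorbidity rule at their index reading, and say what comorbid condition means in the matching.
2. Add baseline BMI to the matching variables. The closeness of the match is for the team to choose.
3. Adjust the routine-care comparison for baseline BMI, and for baseline HbA1c in the glycaemic comparison.

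Selecting comparators on one high index reading brings regression to the mean into that group as well. The index reading should therefore stand in the same relation to selection as the trial baseline does, and the adjustment in step 3 should be kept.

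The cost is a changed database extraction, with no participant burden and no change to the randomised trial. The pool's size is not given, so eight matches each may not be attainable. With independent observations and equal variances, the variance is proportional to 1 + 1/k for k comparators per participant: 1.125 at 8:1 and 1.25 at 4:1. The standard error ratio is √(1.25/1.125) = 1.054, a loss of about 5%.
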